#### Exclusion Criteria

(1) Participants with severe bronchitis, which is difficult to distinguish from pneumonia in the early stage.(2) Participants with acute infectious diseases such as measles, whooping cough, and influenza.(3) Participants with single acute upper respiratory tract infection, suppurative tonsillitis, asthmatic bronchitis, bronchial asthma, bronchiolitis pneumonia, tuberculosis, or tumor.(4) White blood cell count >12.0 × 10^9^/L, or a lot of purulent sputum in the lungs.(5) Participants with severe malnutrition or immunodeficiency.(6) Participants with severe diseases involving the heart, liver, kidney, digestive and hematopoietic system.(7) Allergic to JZOL or Ambroxol Hydrochloride and Clenbuterol Hydrochloride Oral Solution (AHCHOS).(8) Participants who are taking epinephrine, isoproterenol, or other catecholamines.(9) Participants who are taking monoamine oxidase inhibitors or tricyclic antidepressants.(10) Participants who are taking propranolol or other non-selective β-blockers.(11) Participants who are taking large amounts of other sympathetic stimulants.(12) Participants who are deemed unsuitable for inclusion in this study by the researcher.

#### Drop-Out Criteria

(1) Participants who develop an allergic reaction or serious adverse event (SAE) would be withdrawn from the trial according to the doctor’s judgment.(2) Participants with other concomitant diseases occurring during the trial, which affected the assessment of efficacy and safety of JZOL.(3) Participants whom have poor compliance, changed their medication midway, or added drugs prohibited under this study.(4) Any reason breaking the double-blind setting of this clinical trial.(5) After medication, if the total score of cough and expectoration increased by four points or the armpit temperature >38.5°C continued for more than 48 h, or the child developed bronchial pneumonia, the tested medication should be stopped immediately, effective treatment should be given. The child should complete all laboratory tests, be withdrawn from the study, and be considered an invalid case.(6) Participants who are found to have serious violations of inclusion or exclusion criteria after being enrolled in this study.

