#### Inclusion Criteria

(1) Participants with AB under the diagnostic criteria of Western medicine.(2) Those who meet the TCM diagnostic criteria of phlegm-heat stasis in lungs.(3) Participants aged 2–14 years.(4) Cough (day + night) score ≥4 points.(5) Duration of disease ≤48 h, no antibiotics, antitussives, phlegm-reducing drugs, and other Chinese or Western medicine that influence cough has been used before treatment.(6) The informed consent process complies with the regulations, and the legal representative and/or the child (≥8 years old) signs the informed consent.

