##### Secondary Outcome

(1) Area Under Curve (AUC) of cough and expectoration symptom score-time, cough symptom score (Table 3), antitussive onset time, clinical recovery time, and TCM syndrome score (Li, 2015) (Table 4) will be daily recorded and evaluated at the study endpoint.i. Cough disappeared: cough symptom score (daytime + night) ≤1 point, and maintained for 24 h or more.ii. Antitussive onset time: the number of days required for cough symptom score to decrease by one point after taking the medicine.iii. Clinical recovery: cough, expectoration and pulmonary symptoms are all mild after treatment, without affecting study, living and sleep.iv. Evaluation criteria for the efficacy of TCM syndromesA. Clinical recovery: the total score decreased by ≥90%.B. Significant effect: the total score decreased by ≥70% and <90%.C. Effective: the total score decreased by ≥30% and <70%.D. Ineffective: those who fail to meet the above standards.(2) The disappearance rate of cough, sputum and pulmonary rales will be evaluated at the study endpoint.(3) The usage of antibiotics, antipyretics or analgesics will be evaluated at the study endpoint.

**TABLE 3 T3:** Cough symptom scoring.

Score	Daytime symptom	Night symptom
0	No cough	No cough
1	Short occasional cough	Short occasional cough during sleep
2	Frequent cough, daily activities mildly affected	Slight disturbance of sleep due to cough
3	Frequent cough, daily activities severely affected	Severe disturbance of sleep due to cough

**TABLE 4 T4:** Quantitative Grading evaluation for TCM syndrome.

Grading symptoms		(−)	(+)	(++)	(+++)
Primary symptoms		0	1	2	3
Cough	Daytime	No cough	Short occasional cough	Frequent cough, daily activities mildly affected	Frequent cough, daily activities severely affected
	Night	No cough	Short occasional cough during sleep	Slight disturbance of sleep due to cough	Severe disturbance of sleep due to cough
Expectoration	Daytime	No expectoration	Phlegm is whitish and slightly sticky	Phlegm is whitish/yellowish and sticky	Phlegm is yellowish and sticky
	Night	No expectoration	Phlegm is easy to cough out	Phlegm is slightly difficult to cough out	Phlegm is difficult to cough out
Secondary Symptoms		0	1	2	3
Fever (24 h maximum axillary temperature)		≤37.2°C	37.3–37.9°C	38.0–38.5°C	>38.5°C
Thirsty		No	Yes	Yes	Yes
Facial Erythema		No	Yes	Yes	Yes
Dysphoria		No	Yes	Yes	Yes
Scanty dark-colored urine		No	Yes	Yes	Yes
Dry stool		No	Yes	Yes	Yes
Tongue and pulse condition		Normal	Abnormal	Others	

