Tongue		Pinkish	Reddish	—	
Tongue coating		Thin whitish coating	Yellowish coating	—	
Pulse condition		Normal	Slippery and rapid	—	

Note : Children who cannot expectorate is not included.

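### Measured from baseline, the four-point symptom trigger in drop-out item 5 cannot be met by a child who enters with a cough + expectoration total of 9 to 12, because the scale stops at 12

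*Protocol article*

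**What the plan says.** Drop-Out Criteria, item 5, applies once dosing has begun. Study drug is stopped, effective treatment is given and the child is withdrawn as an invalid case "if the total score of cough and expectoration increased by four points". Two other triggers stand beside this one: an axillary temperature above 38.5°C lasting more than 48 h, "or the child developed bronchial pneumonia". The item does not name the score from which the four points are counted.

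The only expectoration scale in the article is in Table 4, "Quantitative Grading evaluation for TCM syndrome". It grades four items from 0 to 3: cough by day, cough at night, expectoration by day and expectoration at night. A note under the table reads "Children who cannot expectorate is not included".

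Inclusion item 4 requires "Cough (day + night) score ≥4 points" and sets no upper limit. Inclusion item 2 admits "Those who meet the TCM diagnostic criteria of phlegm-heat stasis in lungs". Exclusion item 1 removes "Participants with severe bronchitis, which is difficult to distinguish from pneumonia in the early stage", and exclusion item 4 removes children with a lot of purulent sputum in the lungs. Neither exclusion is defined by the Table 4 score.

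Under Secondary Outcome, the cough and TCM syndrome scores "will be daily recorded and evaluated at the study endpoint".

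**The concern.** A stopping rule that needs a fixed rise on a bounded scale fails for anyone who starts too close to the top. Here the rule asks for four points on a 12-point scale, and the trial admits children anywhere from 4 to 12. Item 5 is the only rule in the article that turns worsening cough and sputum scores into stopping study drug. Under the drug-combination guidelines, expectorants, bronchodilators and other antitussive drugs are barred meanwhile. If the symptom trigger cannot operate for the children with the highest entry scores, it is silent for those with the most marked symptoms. What is at stake is the care of individual children. The rule is the same in both blinded arms, so the treatment comparison is not the issue.

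**Working it through.** The plan gives no figure of its own on this point, so the check is a count on its scale.

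**Inputs**
- Required rise: 4 points (Drop-Out Criteria, item 5).
- Items in the total: 4, each scored 0 to 3 (Table 4).
- Entry floor: cough by day + night of at least 4; no upper limit (Inclusion Criteria, item 4).
- Assumption: the rise is measured from baseline.

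**Ceiling.** Maximum total = (3 + 3) + (3 + 3) = 12. Largest possible rise = 12 − baseline total. The trigger can be met only if 12 − baseline ≥ 4, that is, baseline ≤ 8.

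| Baseline total | 4 | 5 | 6 | 7 | 8 | 9 | 10 | 11 | 12 |
|---|---|---|---|---|---|---|---|---|---|
| Largest rise | 8 | 7 | 6 | 5 | 4 | 3 | 2 | 1 | 0 |
| Can reach +4 | yes | yes | yes | yes | yes | no | no | no | no |
| Score patterns with cough ≥ 4 | 3 | 8 | 14 | 20 | 20 | 16 | 10 | 4 | 1 |

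**Patterns.** Cough of at least 4 can arise in 3 + 2 + 1 = 6 ways (totals 4, 5 and 6). Expectoration can arise in 4 × 4 = 16 ways. That gives 6 × 16 = 96 admissible patterns. Those at 9 to 12 number 16 + 10 + 4 + 1 = 31.

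**Cause.** With no entry floor there are 4 × 4 × 4 × 4 = 256 patterns, of which 35 total 9 or more. The gap therefore comes from the ceiling, not from the entry floor on cough.

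**What a total of 9 looks like.** Cough 2 by day and 3 at night, with expectoration 2 and 2, gives 2 + 3 + 2 + 2 = 9. This needs only the middle expectoration grades, so it is not confined to the extreme of the scale.

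**Children who cannot expectorate.** The note to Table 4 can be read in three ways:
- Expectoration is not scored. The total then stops at 6, entry is at 4, 5 or 6, and the largest rise is 2, 1 or 0. The trigger is out of reach for all of them.
- Expectoration is scored 0. Entry totals of 4, 5 or 6 leave room for 8, 7 or 6, and the trigger can be reached through new sputum.
- Such children are not enrolled. The question does not arise.

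**The case against.** The strongest reply accepts the arithmetic and disputes its consequence. Any change-based rule on a bounded scale has a ceiling, and clinical triggers are a reasonable backstop near it. Several routes to care need no score: the fever and pneumonia triggers, withdrawal for an allergic reaction or serious adverse event on the doctor's judgment, withdrawal for concomitant disease, guardian withdrawal for any reason, antibiotics at the doctor's discretion, and adverse-event observation throughout. Treatment lasts only 7 days. All of this stands, and a reader who inferred that high-scoring children are unprotected would be going beyond the document.

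A reader might also infer that these children lose an earlier warning. The article does not support that. Scores are recorded daily, but no review between visits is described, and Table 2 places syndrome scoring, physical examination and diary-card handling at the same visits (day 5 ± 1 and day 7 ± 1). The fever trigger, on its 48 h clock, could act before the first of these.

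The reply is also right that the note on children who cannot expectorate is ambiguous, and that a condensed article may leave its meaning to the full protocol. That part is conditional and adds no weight to the main point.

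Finally, forcing withdrawal on a one-point rise near the ceiling, when a child at 8 needs four, would be hard to defend. That argues for a clinician review there, not for leaving the rule unchanged.

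What the reply does not answer is that a written safety trigger and the written scale it uses are incompatible over part of the admissible range. That is a conflict between two stated elements, not a detail left out.

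**Conclusion.** The point holds in limited form. If the rise is counted from baseline, the symptom trigger of item 5 cannot be met at baseline totals of 9 to 12, where the largest rise is 3 to 0 against the 4 required. If it were counted from a later low, a child who improved and then relapsed could still reach it; the text does not say, and that silence is part of what needs fixing.

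It is tempting to read 31 of 96 as about a third of children. It is a count of score patterns, and no baseline distribution is given. The exclusion of severe bronchitis and heavy purulent sputum may lower the share affected, while the required phlegm-heat syndrome may raise it. Nothing here affects the sample size or the comparison between arms. The change is worth making because it concerns a stopping rule in children and costs little.

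**What to change.** In Drop-Out Criteria, item 5:

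1. State that the rise is measured from the baseline total.
2. Keep the four-point rule for baseline totals of 8 or less.
3. For baseline totals of 9 or more, add a trigger within the remaining room: a rise to 12, or persistence at 12 in a child who entered at 12, prompts a clinician review with discretion to stop study drug and give effective treatment. It is not an automatic withdrawal. The clinical team should set one fixed duration for the trigger.
4. State how expectoration is scored in a child who cannot expectorate. If it is not scored, apply the same review when cough (day + night) reaches or stays at 6.
5. Leave the fever and pneumonia triggers as they are.

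With this change all 31 patterns have a symptom trigger that can operate: 16 + 10 + 4 = 30 through a rise to 12, and 1 through persistence at 12.

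The cost is a few clauses in item 5. The scores are already recorded daily on the diary card, although someone must look at them for the trigger to work between visits. There would be a few extra reviews and possibly a few extra discontinuations, whose missing values would be carried forward in the primary analysis. Their number cannot be estimated from the article.

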### Statistical Analysis

SAS will be used for statistical analysis. Intention-to-treat analysis will be carried out in this trial, which refers to the analysis of all cases that have been randomized and used drugs at least once. All statistical tests are conducted using a two-sided test, and *p* <0.05 would be considered statistically significant. The missing data will be filled up by carrying forward the last measured value in this trial. Covariance analysis is used for the evaluation of the cough disappearance time. The group is taken as a fixed effect, and the baseline value of the cough symptom score is taken as covariance into the model for analysis. The difference between the different values of the two groups and their bilateral 95% confidence intervals are calculated. Then, the lower limit of bilateral 95% confidence intervals and the preset non-inferiority standard are compared to determine whether the test group is inferior to the control group. In addition, the subgroup analysis is performed according to age (2–3 years, 4–7 years, and 8–14 years). Measurement methods and data sets of secondary outcomes are shown in Table 5. In terms of safety, the number of AEs and SAEs during the study will be listed, and their incidence will be calculated.

**TABLE 5 T5:** Secondary outcome.

Secondary outcome	Test method	Data set
Time-lapse analysis of measured value and changed value of cough symptom score	T test is used to compare the differences between groups	FAS^a^
AUC of cough and expectoration symptom score - time		
Onset of cough relief		
Clinical recovery time		
Disappearance rate of cough, expectoration and lung rales	χ2 test or Fisher’s exact probability method is used to compare the differences between groups	
Use of antibiotics, antipyretics and analgesics		
Analysis on the curative effect of TCM syndrome	CMH chi-square is used to compare the differences between groups	

a FAS, Full Analysis Set; AUC, Area Under Curve.

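### Children who worsen are withdrawn under an undefined label and have no usable cough disappearance time, so treatment failures can be lost from the non-inferiority comparison

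*Protocol article*

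**What the plan says.** **Drop-Out Criteria.** Item 5 applies after medication has begun. Its triggers are "if the total score of cough and expectoration increased by four points or the armpit temperature >38.5°C continued for more than 48 h", or the development of bronchial pneumonia. Study drug then stops, and after the laboratory tests the child is to "be withdrawn from the study, and be considered an invalid case". Item 1 covers allergic reactions and serious adverse events; these children "would be withdrawn from the trial according to the doctor’s judgment". Item 3 lists "Participants whom have poor compliance, changed their medication midway, or added drugs prohibited under this study". Other items cover concomitant disease, broken blinding and serious eligibility violations.

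**Statistical Analysis.** The analysis is called intention-to-treat, "which refers to the analysis of all cases that have been randomized and used drugs at least once". For gaps: "The missing data will be filled up by carrying forward the last measured value in this trial". For the primary outcome: "Covariance analysis is used for the evaluation of the cough disappearance time". Table 5 assigns the secondary outcomes to the full analysis set (FAS).

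**Outcome definition and schedule.** Cough counts as disappeared when the day-plus-night score is at most 1 and stays there for at least 24 hours. Scores are kept on a diary card. Treatment lasts 7 days, and the last visit is at day 7 ± 1.

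**The concern.** The item 5 triggers are treatment failure or close to it, so withdrawal under item 5 depends on the outcome. All these children have been dosed, so all belong to the stated analysis set. The article does not say what the item 5 label means for the analysis or what cough disappearance time such a child receives.

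The primary outcome is a time, and the missing-data rule acts on measured values. If failures vanish from the comparison, or enter it as early recoveries, the arm with more of them looks better than it is. In a non-inferiority trial against an active comparator, that error runs towards the claim being tested.

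**Working it through.** **1. The plan's own figure.** Inputs from Sample Size Calculation: margin 0.5 day, SD 2 days, true difference 0, one-sided α 0.025, power 0.95.
- Normal approximation: n = 2 × 2² × (1.960 + 1.645)² / 0.5² ≈ 416 per group.
- Noncentral t: power first reaches 0.95 at n = 417 (0.9501), which matches the stated 417.
- The step to 500 per group implies a withdrawal allowance of 1 − 417/500 = 16.6%.

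**2. What last value carried forward does to a child under item 5.** Carrying forward a worsened score never meets the disappearance definition, so it yields no time. Two outcomes remain if nothing else is specified: the child has no value and leaves the covariance analysis, or the withdrawal day is used as if cough had ended then.

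**3. Size of the bias from exclusion.** Assumptions that are not in the documents: non-failures have mean 5 and SD 2 days in both arms (the planning values, applied here to non-failures); a failure is valued at Tf = 7 or 8 days, the end of the scheduled window; d is the excess failure proportion on JZOL. An arm with failure proportion p has mean 5 + p × (Tf − 5), so excluding failures hides d × (Tf − 5):

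| Excess d | Tf = 7 | Tf = 8 |
|---|---|---|
| 2 points | 0.04 day | 0.06 day |
| 5 points | 0.10 day | 0.15 day |
| 10 points | 0.20 day | 0.30 day |

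At 10 points this is 40% to 60% of the margin. The whole margin is hidden at 0.5/(7 − 5) = 25 points or 0.5/(8 − 5) = 16.7 points.

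**4. Effect on the conclusion.** Simulation with 500 per arm, 4,000 runs per scenario, 5% failures on control and no baseline covariate. The difference is JZOL minus control in days, so non-inferiority requires the upper 95% limit to lie below 0.5. Percentage of trials declaring non-inferiority:

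| Failures, JZOL v control | Excluded | Kept at day 7 | Kept at day 8 | Entered at withdrawal, assumed day 3 |
|---|---|---|---|---|
| 5% v 5% | 97–98 | 98 | 97 | 98 |
| 10% v 5% | 96–97 | 89 | 77 | about 100 |
| 15% v 5% | 96–97 | 66 | 32 | about 100 |

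A repeat set of runs agreed within about 2 points (for 15% v 5%: 65% at day 7 and 34% at day 8).

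**The case against.** **No strict contradiction is shown.** A reader might infer that item 5 removes these children from the analysis, so that it and the intention-to-treat statement cannot both stand. The documents do not go that far. A child can be withdrawn from the study and still belong to the randomised-and-dosed set, and nothing states that the label means exclusion. It appears only on the worsening item, not on non-compliance or eligibility violations, which fits a meaning of treatment ineffective. Against that, the syndrome efficacy criteria already have a separate category for ineffective, and enlarging 417 to 500 suggests that withdrawn children are not expected to contribute data. The term is ambiguous. Even the friendly reading leaves the disappearance time unassigned.

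**Loss of observation is not stated.** A reader might also infer that all other drop-outs leave observation. The section does not say that the diary or visits end, and item 5 requires laboratory tests to be completed. What stands is that continued symptom recording is not secured.

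**The size depends on assumptions.** Entry requires a cough score of at least 4 out of 6, so cough can rise by at most 2 and the four-point trigger also needs expectoration to rise by at least 2. High failure rates cannot be presumed. A reader might also value failures at, say, 10 days, which at 15% v 5% gives 0.10 × (10 − 5) = 0.50 day, the entire margin. That time lies outside the day 7 ± 1 window. Within the window the same scenario gives 0.20 to 0.30 day.

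**Could this be left to the analysis plan?** Detailed handling of withdrawals could. The label and the withdrawal instruction, however, stand in the protocol and direct the sites, and no later plan can recover diary data that were not collected.

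**Conclusion.** The concern holds in a limited form. The Drop-Out Criteria and the Statistical Analysis section are not reconciled for children who worsen: the label is undefined, their primary outcome has no value, and the missing-data rule cannot create one. The resulting bias favours whichever arm has more failures.

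Its size is conditional. With equal failure rates it is negligible. With 5% failures on control and failures valued at day 7 or 8, exclusion hides 0.10 to 0.15 day at a 5-point excess on JZOL and 0.20 to 0.30 day at a 10-point excess. At 10 points, non-inferiority is declared in about 96% of trials if failures are dropped, against about 66% (day 7) or 32% to 34% (day 8) if they are kept. Using the withdrawal day as the outcome would be worse still. The documents give no failure rates, so these figures show what could happen and do not predict it. Equal rates cannot be taken for granted when relative efficacy is the question under test.

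**What to change.** Reconcile the two sections as follows:
- Replace the item 5 label with a statement that these children remain in the FAS and count as cough not disappeared in the disappearance-rate outcomes.
- Pre-specify how they enter the primary analysis. Covariance analysis needs a number, so to call them unresolved is not enough. One option is the last day of the diary window; another is censoring there in a time-to-event sensitivity analysis. The withdrawal day should never serve as the disappearance time.
- State that stopping study drug, for any drop-out reason, does not stop the diary or the scheduled day-7 visit unless consent is withdrawn.

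The clinical stopping rule is not touched and the sample size is unchanged. The cost is protocol wording plus some extra diary cards and attendance at visits already scheduled. One small downside is that the estimate will include children who have moved to other treatment.

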#### Voluntary Withdrawal of Participants

(1) The participants and their guardians are unwilling or unable to continue the trial for any reason and request the physician in charge to withdraw the candidate from the trial.(2) Participants who no longer receive medication and testing, and were lost to follow-up visits.

